# Comparison of conventional, burst and high-frequency spinal cord stimulation on pain relief in refractory failed back surgery syndrome patients: study protocol for a prospective randomized double-blinded cross-over trial (MULTIWAVE study)

**DOI:** 10.1186/s13063-020-04587-6

**Published:** 2020-08-03

**Keywords:** Failed back surgery syndrome, “Paraesthesia free” spinal cord stimulation, Sub-paraesthestic stimulation, Randomized controlled trial, Back pain, Waveform, Chronic pain

## Abstract

**Background:**

While the evolution of technology provides new opportunities to manage chronic refractory pain using different waveform modalities of spinal cord stimulation in failed back surgery syndrome (FBSS), there is no randomized controlled trial available to compare the efficacy of these different stimulations waveforms to date. MULTIWAVE is a prospective, randomized, double-blinded, crossover trial study designed to compare the clinical efficacy of tonic conventional stimulation (TCS), burst stimulation (BURST) and high-frequency stimulation (HF) in FBSS patients over a 15-month period in SCS implanted patients.

**Methods/design:**

Twenty-eight patients will be recruited in the Poitiers University Hospital, in Niort and La Rochelle Hospitals in France. Eligible patients with post-operative low back and leg pain with an average visual analog scale (VAS) score ≥ 5 for low back pain are implanted and randomly assigned to one of the six arms (in a 1:1:1:1:1:1 ratio), where they receive a 3-month combination of TCS, BURST and HF including one treatment modality per month and varying the order of the modality received within the six possible combinations. Patients receiving intrathecal drug delivery, peripheral nerve stimulation and back resurgery related to the original back pain complaint and experimental therapies are excluded from this study. Patients included in the spinal cord stimulation group undergo trial stimulation, and they all receive a TCS treatment for 2 months, as the gold standard modality. Thereafter, patients are randomly assigned to one of the six arms for the total duration of 3-month crossover period. Then, patients choose their preferred stimulation modality (TCS, BURST, or HF) for the follow-up period of 12 months. Outcome assessments are performed at baseline (first implant), before randomization (2 months after baseline) and at 1, 2, 3, 6, 9 and 15 months post-randomization. Our primary outcome is the average global VAS of pain over 5-day pain diary period between baseline and after each period of stimulation. Additional outcomes include changes in leg and back pain intensity, functional disability, quality of life, psychological state, paraesthesia intensity perception, patient satisfaction and the number of adverse events.

**Discussion:**

Recruitment began in February 2017 and will continue through 2019.

**Trial registration:**

Clinicaltrials.gov NCT03014583. Registered on 9 January 2017.

## Background

Failed back surgery syndrome (FBSS), defined by chronic back and/or leg pain after lumbosacral spine surgery [1–5], is reported for 5–55% of the patients post-operatively [6]. FBSS is characterized by mixed neuropathic and nociceptive pain components described as refractory. Pain is defined as refractory, regardless of aetiology, when (i) multiple evidence-based biomedical therapies used in a clinically appropriate and acceptable fashion have failed to reach treatment goals, which may include adequate pain reduction and/or improvement in daily functioning, or have resulted in intolerable adverse effects, and when (ii) psychiatric disorders and psychosocial factors that could influence pain outcomes have been assessed and appropriately addressed [7]. FBSS can have a dramatic impact on functional ability, social aspects and quality of life, resulting in a considerable financial burden on the society [8].

Studies have clearly demonstrated the clinical efficacy and medico-economic interest of spinal cord stimulation (SCS), which consists in delivering an electrical current to the dorsal epidural space via electrodes, as a way of managing refractory pain in FBSS patients [9, 10]. However, the most widely studied and used technique for SCS remains tonic conventional stimulation (TCS), delivering low frequencies (< 100 Hz), which does not appear to relieve pain in more than 30–55% of FBSS patients [9–11]. Moreover, low-frequency SCS provokes paraesthesia, which can ultimately be perceived by some implanted patients as an uncomfortable sensation [12]. These findings have compelled the industry to investigate new sub-paraesthetic stimulation modalities, such as burst (BURST) and high-frequency (HF) stimulation waveforms [13].

Recent clinical trials provide evidence for the efficacy of BURST [14–17] and HF [18–21] SCS in FBSS patients. The main added values of BURST and HF SCS could lead to the elimination of paraesthesia and have a synergistic effect by targeting different intra-spinal structures, mechanisms of action and brain cortical areas in comparison with TCS [22]. RCT evidence is clearly needed to compare the efficacy of TCS, BURST and HF modalities in FBSS patients implanted with new generation SCS.

### Aims and objectives

The MULTIWAVE study is an RCT comparing clinical SCS efficacy using TCS, BURST and HF modalities in a crossover design in implanted chronic refractory FBSS patients. Before randomization, all implanted patients receive TCS treatment for 2 months. Then, TCS, BURST and HF waveforms are randomly and alternatively administered for a 1-month period and a total duration of 3 months for the three different SCS waveforms. After the 3-month period, each patient selects his or her preferred stimulation modality with a follow-up period of 12 months.

The primary objective of this study is to compare the efficacy of TCS, BURST and HF Stimulation on pain relief (measured using a visual analog scale) in refractory FBSS patients. Secondary objectives are to compare changes in the following outcomes for each of the three treatment modalities: back pain intensity, leg pain intensity, functional disability, quality of life and psychological state.

## Methods/design

This protocol is reported in accordance with the SPIRIT 2013 guidelines for protocols of clinical trials [23].

### Design and setting

MULTIWAVE study is a prospective, controlled, randomized, crossover, double-blind trial comparing TCS, BURST and HF SCS treatments. Twenty-eight patients will be recruited in the Poitiers University Hospital, in Niort and La Rochelle Hospitals in France. Patients will be implanted with a 32-contact surgical lead and a Precision Spectra SCS System™ (Boston Scientific Inc., Valencia, USA) Internal Pulse Generator (IPG) enabling use of these different waveforms. After a period of 2 months following the surgical lead implant, patients will be randomized 1:1:1:1:1:1 to various SCS modalities. During this period, patients will receive a 3-month specific set of 3 combinations of TCS, BURST and HF amongst 6 possible combinations, delivering each treatment modality during a 1-month period. Patients will be unable to switch from one waveform to another modality until the end of the crossover period. After completion of the 3-month post-randomization period, patients will be asked to choose their preferred SCS modality. Starting with this visit, patients will be able to switch from a waveform to another depending on daily activity within a day. In case the choice of waveform is not obvious, to assist decision making, the patient will be allowed to see his VAS score and pain mapping. Reasons for modality choice will be collected. Patients are monitored up to 15 months post-randomization. The study design is presented in Fig. 1.

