### Primary outcome

The primary outcome is the variation of average global VAS score, assessed over a 5-day pain diary, between baseline (randomization, M0) and after each treatment period [31]. Patients record their global, back and leg pain using a (paper) pain diary once a day, for a 5-day period within 1 week prior to each scheduled study visit.

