### Statistical analysis

Categorical variables will be described by numbers and percentages while quantitative variables will be described by the mean and its confidence interval or median and interquartile range based on the skewness of the variable. The study sample will be described by age, gender, BMI, duration between pain appearance and device implantation, number of spinal surgeries and type of pain (neuropathic/mechanical). The primary hypothesis of the difference between TCS, BURST and HF will be verified using the Friedman test or repeated measures ANOVA depending on the normality of the global pain VAS (average VAS over the 5-day diary period). Shapiro-Wilk test will be used to test for non-normality of distributions. In case the Friedman test indicates significance, a post hoc test using the procedure described by Conover [39] and the Bonferroni *p* value adjustment method will be conducted for pairwise comparisons. Ordinal outcomes will be compared between groups using the same previously described procedure. Quantitative normally distributed endpoints will be compared between groups using repeated measures ANOVA. Pairwise comparisons will be conducted after the repeated measures ANOVA indicate significance. Binary outcomes will be compared using the Cochran Q test and a McNemar test will be conducted for pairwise comparison after the Cochran Q test rejects the null hypothesis.

After the end of the crossover design, patients will choose a preferred waveform and will be followed for 1 year. The proportions of waveform preference will be compared using a chi-square goodness of fit test. The categorical variables will be compared between visits M6, M9 and M15 and baseline using the McNemar test while the continuous variables will be compared between baseline and the post crossover visits using the paired *t* test or Wilcoxon signed-rank test depending on the variables’ distribution. All comparisons will be two-sided with a level of significance of 0.05. Missing data will be described. Patients with missing data on the primary outcome will be excluded from the analysis. The blind analysis is aimed to be conducted in per-protocol analysis. A robustness analysis including all available data will be conducted on the primary outcome using a Skillings-Mack Test. R software will be used for statistical analysis.

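### Undecided patients may see their own VAS scores before stating the preference that is then tested, so the preference test is not fully separate evidence from the VAS comparison

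*Protocol article*

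**What the plan says.** Design and setting in the protocol article describes the end of the crossover: "After completion of the 3-month post-randomization period, patients will be asked to choose their preferred SCS modality". It adds a provision for patients without a clear choice: "to assist decision making, the patient will be allowed to see his VAS score and pain mapping". The display is there to help the patient decide, so it comes before the choice is settled. The same section states that "Reasons for modality choice will be collected".

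Statistical analysis then makes the choice the subject of a formal test: "The proportions of waveform preference will be compared using a chi-square goodness of fit test". The general rule on level applies to it: "All comparisons will be two-sided with a level of significance of 0.05".

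The VAS is also the trial's main endpoint: "The primary outcome is the variation of average global VAS score, assessed over a 5-day pain diary". Preference appears neither among the aims and objectives nor among the secondary outcomes; its formal role is that one sentence on the test.

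**The concern.** A goodness-of-fit test on preference is useful because preference can reflect things that the pain score does not capture. The Discussion makes this point itself: it cites a crossover study in which half the patients kept tonic stimulation for its sensation, while the other half chose burst or high frequency for greater pain relief. If an undecided patient is shown which waveform gave the lowest VAS and then chooses, the choice tends to reproduce the VAS ranking.

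Indecision is foreseeable. The article expects patients to feel no paraesthesia with either burst or high frequency, and its power simulation assumes that these two are equally effective.

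What is at stake is how the preference result can be read. A significant chi-square next to a significant VAS comparison looks like two findings that support each other. To the extent that choices were aided, the second is derived from the first. An undecided patient's lack of preference may also end up counted as a preference.

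**Working it through.** **Inputs from the article (Sample size and power calculations).** VAS means: TCS 5.0, BURST 3.0, HF 3.0. SDs: 2.5, 3.0, 3.0. Correlation 0.60 between any two treatments. 28 patients.

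**Step 1: reproduce the article's own figures.** SD of the TCS–HF difference = √(3.0² + 2.5² − 2 × 0.6 × 3.0 × 2.5) = √6.25 = 2.5, as stated. A simulation of 100,000 trials from this multivariate normal gives Friedman power of 96.1% for 28 patients and 91.1% for 23, against 96.1% and 90.9% stated. The scenario is read correctly. The article gives no figure for the preference test.

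**Step 2: which waveform has the lowest VAS?** Under this scenario the lowest score falls on TCS in 8.6% of patients and on BURST and HF in about 45.7% each.

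**Step 3: mix aided and unaided choices.** Let u be the undecided share. Assume that decided patients choose at random and that undecided patients take the waveform with their lowest VAS. The expected TCS share is (1 − u)/3 + u × 0.086:

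- u = 20%: 0.267 + 0.017 = 28.4%
- u = 40%: 0.200 + 0.034 = 23.4%
- u = 60%: 0.133 + 0.052 = 18.5%

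BURST and HF share the rest equally. Without aided choices each waveform has 33.3%.

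**Step 4: rejection rate of the chi-square test (28 patients, 2 degrees of freedom, 0.05).** Two assumptions about who is undecided were simulated:

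| Undecided share | Undecided are a random subset | Undecided are those with the smallest VAS range across waveforms |
|---|---|---|
| 0% | 4.5% | 4.5% |
| 20% | 6.6% | 5.2% |
| 40% | 14.1% | 9.1% |
| 60% | 29.9% | 21.0% |

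The second column reflects that a patient whose choice is not obvious may have felt little difference between waveforms. At 10% undecided the random-subset figure is about 5%, which is negligible.

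As a check on the 60% random-subset entry, the noncentrality is 28 × 3 × [(0.185 − 0.333)² + 2 × (0.4075 − 0.333)²] ≈ 2.8. A noncentral chi-square with 2 degrees of freedom then gives a rejection probability of about 30%.

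**Step 5: no VAS difference.** With equal means and SDs for the three waveforms, rejection stays at about 4–5% whatever the undecided share.

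**The case against.** Choosing a waveform is first of all a treatment decision for follow-up, and helping an undecided patient with his own data serves that decision. The scores are not foreign to him: "Patients record their global, back and leg pain using a (paper) pain diary once a day". Pain relief is a proper reason to prefer a waveform, so an informed preference is a legitimate quantity. The display also covers pain mapping, which is not the primary outcome. All of this stands. It argues for labelling the result as informed preference, and it does not make that result separate from VAS.

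The simulation leans towards a large effect. It lets decided patients choose at random despite a real 2-point benefit, and it lets every undecided patient follow the lowest score. That also stands, and it is why a range is given.

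Some stronger readings are tempting but not supported:

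- A reader might infer that undecided patients are allocated a waveform. They choose, and from that visit they may switch within a day.
- A reader might infer that the form has no option for having no preference, or that aided and unaided choices are certainly pooled. The article is silent on both. The case report form, full protocol or analysis plan may deal with them.
- A reader might infer that preference is to be presented as evidence independent of VAS. The article nowhere says so.

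The collected reasons for choice may help interpretation, but the article does not say that they identify who saw the scores. An analysis plan could separate aided from unaided choices only if the visit had recorded the difference.

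**Conclusion.** The point holds as a minor one. The order of events is stated in the article: an undecided patient may see primary-outcome data, then chooses, and the choices are tested. For those patients the test partly carries the VAS result.

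Under the article's VAS scenario the rejection rate rises from 4.5% to about 5–7%, 9–14% or 21–30% at 20%, 40% or 60% undecided. These figures assume random choice by decided patients and score-following by undecided ones. The undecided share is not given, and at 10% the effect is negligible.

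It would be wrong to call this a test that produces false positives on its own. Without a VAS difference the level stays at 4–5%, so the issue is dependence between two results. The primary comparison is untouched, because its data are complete before any scores are shown, and preference is not a listed objective or outcome.

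**What to change.** At M3, record the patient's unaided preference, with 'undecided' as an allowed answer, before any scores or maps are shown. Then show them, as now, to help choose the follow-up programme. Flag each aided choice. Report the chi-square test on unaided choices and on all choices, label the second as informed preference, and give the number undecided.

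Trial status puts the end of recruitment in December 2019. Adding the 2 months of tonic stimulation and the 3-month crossover brings the last M3 visits to about May 2020, before the article appeared in August 2020, so most or all are probably done. In that case, identify the patients who were shown their scores as far as records allow, report the test with and without them, and state how many there were.

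The cost is one extra form item, a sentence in the analysis section, and fewer than 28 patients in the unaided test. Leaving aided patients out altogether is debatable, which is why both results should be shown.

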**Fig. 1 Fig1:**
[figure not shown]
MULTIWAVE trial patient flow

### Patient selection

The study population comprises patients suffering from chronic significant low back and leg pain following spinal surgery (so called “FBSS”). A patient must meet all the inclusion criteria and none of the exclusion criteria to be eligible for the study. Inclusion/exclusion criteria will be checked by the Principal Investigator, who is an expert neurosurgeon specialized in surgical SCS implantation.

### Inclusion criteria

The patient is an eligible candidate for SCS, according to the French guidelines for SCS selection and implantation (an average 7-day trial period was completed after lead implantation in all patients assigned to receive SCS). The pain should be refractory despite well-conducted conservative management and no further spine surgery required. For the purposes of this study, FBSS is defined as persistent or recurrent low back and leg pain of at least 6 months’ duration, following at least one decompression and/or fusion procedure [1–5]. The patient has persistent low back and leg pain despite other treatment (pharmacological, surgical, physical, or psychological therapies) that have been tried and did not prove satisfactory, are unsuitable, or are contraindicated for the subject, comprising documented neuropathic characteristics of the radicular and/or low back pain component (Neuropathic pain Diagnostic questionnaire (DN4): sensorimotor testing, clinical examination, pain characteristics, etc.), and presents average back pain ≥ 50 mm over 100 mm, where 0 mm represents no pain and 100 mm the worst imaginable pain, as assessed by the baseline visual analog scale (VAS). Mean daily VAS score calculated on 5 consecutive days.

### Exclusion criteria

The patient is treated or has previously been treated with SCS, subcutaneous or peripheral nerve stimulation, treated with an intrathecal drug delivery system or requires back surgery at the location related to his/her original back pain complaint or receives/had received experimental therapies; had most recent back surgery less than 6 months ago; presents low back pain accessible to etiological “mechanical” surgical treatment (discogenic low back pain, vertebral instability, spinal deformity, etc.); is < 18 years or > 80 years of age; presents a surgical, anaesthetic or psychiatric contraindication to implantation of a SCS system; is pregnant or planning to become pregnant during the course of the study; would be unable to operate the SCS equipment, based on the opinion of the principal or sub-investigator; and is a member of a vulnerable population.

A patient is considered enrolled in the study upon completion of the informed consent process. The subject records his/her global, back and leg pain scores during a 5-day pain diary period prior to randomization. FBSS diagnosis and candidacy for SCS is confirmed based on appropriate imaging according to usual practice. In addition, in cases where psychological and anaesthetic evaluations are standard of care and/or required, the evaluations must take place prior to randomization.

### Interventions

Subjects who meet the inclusion criteria and none of the exclusion criteria undergo a 7-day SCS screening trial period with a CoverEdge 32-contact surgical lead™ implantation (Fig. 2).

**Fig. 2 Fig2:**
[figure not shown]
An artistic view illustrating SCS implantation with a 32-contact surgical lead. TCS, BURST and HF waveforms are described by frequency, pulse width and amplitude

The implantation procedure describes the various steps of the surgery until final implantation of the 32-contact surgical lead. Procedure length is about 60 min.

#### Phase 1: 32-contact surgical lead insertion

For this procedure, in order to optimize patient cooperation, patients will be placed in prone position and implanted under Target controlled IntraVenous Anaesthesia (TCIVA) allowing patient feedback or general anaesthesia. A CoverEdge 32-contact surgical lead will be implanted empirically at T8/T9 vertebral level, using a minimally invasive technique according to our usual practice. The projection of the conus medullaris over L1-L2 will be assessed on pre-operative MRI, previously to lead implantation to ensure optimal localization of the surgical lead. Immediate fluoroscopic control of the vertebral projection, the lateralization of the lead and lead impedance check will be performed.

#### Phase 2: Electrophysiological testing and “sweet spot” intra-operative mapping for patients under awake anaesthesia by TCIVA only

After radiological assessment of the lead positioning by X-rays, preliminary lead electrophysiological testing will be performed and the lead will subsequently be navigated longitudinally through the epidural space, to determine the best vertebral level and implantation site, using patient feedback and objective quantitative measurements by tactile interface mapping data (NeuroMapping Tools Software) [24, 25]. The goal of the lead implantation is to address the sweet spot location (an anatomical area located within the dorsal columns (DC) of the spinal cord), able when electrically stimulated to generate significant paraesthesia in the appropriate back dermatoma.

#### Phase 3: 32-contact lead programming testing (for patients under awake anaesthesia by TCIVA only)

Some TCS patterns will be tested using various predetermined combinations, in order to achieve good pain coverage, by targeting the sweet spot location with objective quantitative measurements by tactile interface mapping data (NeuroMapping Tools Software) [24, 25]. This is facilitated by our integrated operating theatre, dedicated to SCS implantation, including several of the new computer-assisted and imaging-assisted technologies (multiple screens with live wall projection, full HD camera filming patient feedback and C-arm screen implementation, HF microphones and earphones enhancing surgeon/patient per-operative interactions).

